## 2.3. Potential Risks and benefits:

### a. End Points – Efficacy

There is the potential benefit to study participants in either control or experimental groups that the prime-boost-boost vaccine combination they receive will provide enhanced long-term humoral and cellular immunity (compared with not receiving a booster) against wildtype SARS-CoV-2 and/or 1 ≥ VOC.

For the wider community, it is expected that the information gained from this study may contribute to the development of a versatile, safe and effective vaccination programme against COVID-19.

### b. End Points – Safety

The COVID-19 vaccines to be used in this study have proven efficacy and safety. It is possible that study participants in the experimental groups may be less well protected against SARS-CoV-2 infection compared with the control group, however, all participants are expected to receive a significant boost to protective immunity.

Similarly, based on extensive studies conducted overseas, no additional safety risks with the prime-boost-boost combinations are expected, including antibody-dependent enhancement or immunopathology as these were not observed as part of the clinical trials of the primary vaccine series. Safety of the prime-boost-boost vaccinations will be assessed by monitoring the incidence of SAEs and AEs. See product inserts for specific risks from individual vaccines.

Of the study procedures, phlebotomy may be associated with localised bruising and discomfort at the site of venepuncture. Infrequently fainting may occur. These will not be documented as AEs as may occur with any venepunctures and are not related to study products. The total volume of blood drawn over a 12-month period is less than 200mL, within limits recommended by DSRB for otherwise healthy volunteer adults.

## 3. STUDY POPULATION

### 3.1. List the number of subjects to be enrolled.

The maximum feasible target will be 100 participants per intervention group of the prime-boost-boost COVID-19 vaccination. A total of up to 600 participants was planned at the outset of this study, and 150 were enrolled across Phases A to C.

For Phase D we will enrol 250 individuals (see section 6). The recruitment period has been extending to 1 year and the follow-up period is 1 year.

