## 5. STUDY DESIGN

### 5.1. Summary of Study Design

PRIBIVAC is an adaptive, randomised, subject-blinded, controlled trial to assess the immunogenicity and safety of heterologous boost COVID-19 vaccination (intervention groups) compared with a homologous boost regimen (control group). For phases A-C of the study potential participants would have already received the second dose of a homologous prime-boost vaccination with BNT162b2 or mRNA-1273 at least six months prior to enrolment. For Phase D a booster dose of either BNT162b2 or mRNA-1273 would have been administered at least five months prior to enrolment.

In Phase A-C of the study the booster vaccine for the control arm will be the homologous mRNA vaccine (e.g. BNT162b2 + BNT162b2 + BNT162b2 or mRNA-1273 + mRNA-1273 + mRNA-1273), while for individuals randomised to intervention group 1 the mRNA booster vaccine administered will be heterologous to the primary series (e.g. BNT162b2 + BNT162b2 + mRNA-1273 or mRNA-1273 + mRNA-1273 + BNT162b2). The booster vaccine candidates for intervention groups 2 and 3 were an alternative COVID-19 vaccine.

Control group: Homologous mRNA booster vaccine

Intervention group 1: Heterologous mRNA booster vaccine

Intervention group 2: Non-mRNA booster vaccine A (i.e. COVAXIN®)

Intervention group 3: Non-mRNA booster vaccine B (i.e. Nuvaxovid)

Phase D of the study will examine the immune response following a second COVID-19 vaccine booster. Study participant will be randomised to receive one of three vaccines in equal proportions: Comirnaty or Comirnaty Bivalent (Original/Omicron BA.4/5), Moderna/Spikevax or Moderna/Spikevax Bivalent (Original/Omicron BA.1) or Nuvaxovid. Vaccines are obtained from the Singapore Ministry of Health stockpile. Where possible the bivalent Comirnaty/Spikevax vaccines will be administered to study participants, however, because of uncertainties in availability the monovalent may be administered if bivalent stock is not available in Singapore. For analysis the reference point for determining homologous and heterologous vaccination regimen may include the primary vaccine series or first booster.

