## **6. METHODS AND ASSESSMENTS**

### **6.1. Randomisation and Blinding**

Randomisation will be performed using a web-based randomisation system hosted by Singapore Clinical Research Institute (SCRI), in which a randomisation list with randomised permuted blocks will be generated by the trial statistician. Password secured accounts will be assigned to the site personnel who are responsible for the randomisation, where he/she can log into the randomisation system using the Internet.

For the first booster part of the trial randomisation will be stratified by the following criteria:

1. Age (<60, ≥60)
2. Primary vaccine series (BNT162b2 or mRNA-1273)
3. Time from 2nd vaccine dose administered (6-9 months, >9 months)

For the second booster part of the trial randomisation will be stratified by the following criteria:

1. Age (<60, ≥60)
2. Primary vaccine series (BNT162b2 or mRNA-1273)
3. First booster vaccine received (BNT162b2 or mRNA-1273)

Eligible participants will be randomised in equal proportions to each of the study arms that are open for randomisation. Enrolment to a study arm will be discontinued if recommended by DSMB or if the target sample size of 100 in the study arm has been reached. In the scenario where recruitment is discontinued in any of the intervention arms from 1 to 4 at the interim analysis, randomisation to the control arm may continue beyond 100 participants until the target sample size of 100 participants has been reached in the remaining intervention arms.

Allocation concealment will be maintained until the registration and randomisation process have been completed. For Phase A-D of the study, vaccine allocation will be single-blind, i.e. only participants will be blinded. Blinding will be maintained for the participants till their Day-28 Visits (Visit 3).

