## **11. SAMPLE SIZE AND STATISTICAL METHODS**

### **11.1. Determination of Sample Size**

Based on the data from our ongoing COVID-19 vaccine immune-monitoring study (SCOPE), the mean level of SARS-CoV-2 anti-spike immunoglobulins was 84% (SD=15%) at 28 days after the second dose. This was determined using a SARS-CoV-2 surrogate virus neutralisation test (sVNT) that detects total immuno-dominant neutralising antibodies targeting the viral spike (S) protein receptor-binding domain in an isotype- and species-independent manner. We expect immunogenicity will be boosted back to the same level after the booster dose in the control arm. With an assumed immunogenicity level of 81% in an intervention arm and a non-inferiority margin of -10%, a sample size of 87 subjects per arm will ensure concluding non-inferiority of the intervention arm against the control arm with 80% power. The sample size is calculated at a one-sided 2.5% significance level and allows for a 15% dropouts. A sample size will offer power of 85.1% based on the above parameters.

Since recruitment of subjects to intervention arms may be activated in a staggered way depending on availability of the vaccines, and recruitment to the control arm will continue until the target

sample size of 100 is achieved in each intervention arm, we prepare to enrol a double sample size in the control arm for the purpose of study planning. This gives a total sample size of up to 600 subjects.

For Phase D of the study, the objective is to estimate the mean difference in humoral immunity (log10-transformed anti-S at day 28) between Pfizer vs Moderna, Pfizer vs Nuvaxovid and Moderna vs Nuvaxovid received as 2nd booster (three mean difference estimations). No hypothesis testing will be performed.

The standard deviation of day 28 log10-transformed anti-S titre from Phase A of the study was assumed to apply to responses to the second booster (note data from those aged 60 years and above per current MOH advisory for a second COVID-19 booster). Using confidence interval approach for sample size calculation, a sample size of 50 per arm (after allowing 5% dropout rate) was estimated to produce two-sided 95% confidence interval with distance from difference in means to limits that is equal to 0.13 when standard deviation of log10-transformed anti-S titre is assumed to be 0.32 for both arms that is being compared.

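### Phase D is set at 250 participants in section 3.1, but its only sample-size calculation (section 11.1) supports 150, and the stated ±0.13 precision belongs to 150

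*Protocol*

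**What the plan says.** Four places in the protocol bear on the size of Phase D.

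- **Section 3.1** gives the enrolment: "For Phase D we will enrol 250 individuals (see section 6"). It also sets a one-year recruitment period and describes 100 per intervention group as the most that is feasible.
- **Section 5.1** gives the allocation. Participants are "randomised to receive one of three vaccines in equal proportions".
- **Section 11.1** gives the only Phase D calculation: "a sample size of 50 per arm (after allowing 5% dropout rate) was estimated to produce two-sided 95% confidence interval", with a "distance from difference in means to limits that is equal to 0.13" when the "standard deviation of log10-transformed anti-S titre is assumed to be 0.32 for both arms" being compared. The aim is to estimate three pairwise mean differences in log10 anti-S at day 28, and "No hypothesis testing will be performed".
- **Section 6.1** closes an arm on a DSMB recommendation or "if the target sample size of 100 in the study arm has been reached". The sentence follows the stratification lists for both the first-booster and second-booster parts and names no phase.

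**The concern.** Three equal arms of 50 make 150, not 250. Dropout cannot account for the gap, because section 11.1 has already allowed for it. A reader who follows the pointer in section 3.1 to section 6 finds no 250 and no derivation; the only target there is the 100-per-arm closing figure.

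This matters because interval width is the only justification offered for the size of Phase D: there is no test, no margin and no power statement. If the enrolment and the calculation describe different trials, the stated size has no justification and the stated precision is attached to a size that section 3.1 does not plan. An ethics committee would also expect a reason for 100 further people being vaccinated, bled repeatedly and followed for a year.

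**Working it through.** **Inputs, all from the protocol.** Standard deviation 0.32 on log10 anti-S in each arm, half-width 0.13, two-sided 95% interval and 5% dropout (section 11.1); three arms, equal allocation (section 5.1); total 250 (section 3.1).

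**Formula.** For the unadjusted difference of two means with n evaluable per arm:

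half-width = 1.96 × SD × √(2/n), so n = 2 × (1.96 × SD / half-width)².

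**Step 1: reproduce the figure in section 11.1.**

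- n = 2 × (1.96 × 0.32 / 0.13)² = 46.6, rounded up to 47 evaluable per arm.
- Allowing for dropout: 47 / 0.95 = 49.5, rounded up to 50 per arm.
- A t quantile in place of 1.96 gives 48 evaluable and 51 enrolled, a difference of one.

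The 50 per arm and the 0.13 agree with each other.

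**Step 2: the total this implies.** 3 × 50 = 150. Section 3.1 exceeds it by 250 − 150 = 100, which is 100/150 = 67% more than the calculation supports.

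**Step 3: the precision at each total**, with evaluable n = (total / 3) × 0.95.

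| Phase D total | Per arm | Evaluable per arm | Half-width (normal) | Half-width (t) | Fold-range on the ratio of geometric means (normal) |
|---|---|---|---|---|---|
| 150 | 50 | 47.5 | 0.129 | 0.130 | 10^0.1287 = 1.34 |
| 250 | 83.3 | 79.2 | 0.100 | 0.1005 | 10^0.0997 = 1.26 |

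**Step 4: could other inputs lead from 0.13 to 250?**

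- With 79.2 evaluable per arm, a half-width of 0.13 corresponds to SD = 0.13 × √(79.2/2) / 1.96 = 0.42, not 0.32.
- Keeping SD 0.32 and 47 evaluable, enrolling 83.3 per arm would imply dropout of 1 − 47/83.3 = 44%, not 5%.

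Neither value appears in the protocol.

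**Step 5: the pointer and the closing rule.** Section 6 covers randomisation, pregnancy testing and visits, and does not mention 250. The 100-per-arm rule in section 6.1 is worded with a DSMB, a control arm, an interim analysis and intervention arms 1 to 4. Phase D has no DSMB (sections 5.1 and 9.4), its interim analyses are described for Phases A-C only (section 11.2 d), and it is analysed by pairwise comparison rather than against a control arm (section 11.2 c). The rule therefore reads as Phase A-C text whose scope was not limited when Phase D was added.

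**The case against.** The strongest reply is that the error does no harm. The calculation in section 11.1 is right on its own terms, and enrolling 250 meets and exceeds the precision it promises. Phase D results are labelled exploratory, no test is planned, and no margin or power depends on the number. All of this stands. It bears on how serious the point is, but it does not make 250 and 150 the same trial.

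A reader might infer three stronger claims, which the protocol does not support:

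- **A third Phase D target of 300 (3 × 100).** That total is nowhere stated for Phase D. The 100 is Phase A-C wording in section 6.1 and a ceiling in section 3.1. With 250 split equally, each arm reaches about 83, so the ceiling does not bind and does not contradict 250. What can fairly be said is that section 6.1 does not limit the rule to a phase and gives Phase D no closing number of its own.
- **Enrolment has no fixed end, or could stop anywhere from 150 to 300.** Section 3.1 fixes both a number and a one-year recruitment period. Stopping at 150 would fall short of that number and enrolling 300 would exceed it. Section 11.1 is a precision calculation, not a stopping rule. The study team is unblinded, but there is no Phase D test whose error rate the choice of stopping point could inflate.
- **An explanation for 250.** Five authorised products at 50 each make 250. But sections 5.1 and 11.1 define three arms and three comparisons, and whether a bivalent or monovalent product is given depends on stock, so no per-product target is set. The calculation also draws its standard deviation from participants aged 60 and above, whereas section 1.2 describes a later recommendation for all adults. That may mean section 3.1 was updated and section 11.1 was not, but the protocol does not say so.

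Nor is it a defect that 250 does not divide by three: stratified permuted blocks do not guarantee exactly equal arms.

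**Conclusion.** The point holds as an inconsistency in a basic design figure. Section 3.1 sets Phase D at 250, the only calculation supports 150, the difference of 100 is unexplained, and the cross-reference to section 6 supports neither. The half-width of 0.13 is correct for 150; at 250 it would be about 0.10. On the ratio scale the expected interval runs a factor of about 1.34 either side of the estimate at 150, against 1.26 at 250.

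The effect is conservative if 250 is what is enrolled, and it touches exploratory estimates only. The figures assume a standard deviation of 0.32 in each arm, 5% dropout, equal allocation and an unadjusted comparison. The regression planned in section 11.2 adjusts for baseline level and stratification factors, so the realised widths may differ. The protocol does not show which of the two totals the sponsor intends.

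**What to change.** 1. Decide the Phase D total, and state it with the per-arm number in both section 3.1 and section 11.1.
2. Give the matching half-width in section 11.1 at SD 0.32 and 5% dropout: 0.13 for 150 (50 per arm), or about 0.10 for 250 (83 to 84 per arm). If 250 is kept, add the reason for choosing that precision or that number.
3. In section 3.1, point to section 11.1 instead of section 6.
4. In section 6.1, limit the 100-per-arm closing rule to Phases A-C and give Phase D its own closing number, consistent with step 1.

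The cost is a text amendment. If 250 is intended, no one is enrolled beyond what section 3.1 already states; if 150 is intended, planned enrolment falls by 100.

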### **3.2. Criteria for Recruitment**

For phases A-C the key eligibility criterion was individuals who had received a homologous primary vaccines series with BNT162b2 or mRNA-1273 at least six months prior. For Phase D, the key eligibility criteria will be receipt of an mRNA booster vaccine at least five months prior.

### **3.3. Inclusion Criteria**

1. Willing and able to provide informed consent for participation in this study;
2. Aged  $\geq 21$  years at the time of study enrolment;
3. Received the second dose of BNT162b2 or mRNA-1273 Coronavirus Disease 2019 vaccines at least 6 months prior to enrolment;
4. Willing and able to comply with all scheduled visits, vaccination plan, laboratory tests and other study procedures.

For Phase D inclusion criteria 3 will be amended to 'Received the first booster dose of BNT162b2 or mRNA-1273 Coronavirus Disease 2019 vaccine at least 5 months prior to enrolment'. Only individuals recommended to receive a second booster dose under MOH recommendations will be enrolled.

### **3.4. Exclusion Criteria**

1. Known history of SARS-CoV-2 or SARS-CoV-1 infection;
2. Previously received an investigational coronavirus vaccine;
3. Previously received a SARS-CoV-2 monoclonal antibody;
4. Current or planned simultaneous participation in another interventional study;
5. A history of anaphylaxis, urticaria, or other significant adverse reaction requiring medical intervention after receipt of a COVID-19 vaccine, or otherwise have a contraindication to one of the available study vaccines per the approved label;
6. Individuals who are immunocompromised (e.g. active leukaemia or lymphoma, generalised malignancy, aplastic anaemia, solid organ transplant, bone marrow transplant, current radiation therapy congenital immunodeficiency, HIV/AIDS with CD4 lymphocyte count  $< 200$  and patients on immunosuppressant medications);
7. Received systemic immunosuppressants or immune-modifying drugs for  $>14$  days in total within 6 months prior to Screening (for corticosteroids  $\geq 20$  milligram per day of prednisone equivalent). Topical tacrolimus is allowed if not used within 14 days prior to Day 1;
8. Individuals who are pregnant or breast feeding;
9. Chronic illness that, in the opinion of the study team, is at a stage where it might interfere with trial conduct or completion;
10. Deprived of freedom by an administrative or court order, or in an emergency setting, or hospitalised involuntarily;
11. Current alcohol abuse or drug addiction that might interfere with the ability to comply with trial procedures in the opinion of the study team;
12. Moderate or severe acute illness/infection (according to study team's judgement) on the day of vaccination, or febrile illness (temperature  $\geq 37.5^{\circ}\text{C}$ ). A prospective participant should not be included in the study until the condition has resolved or the febrile event has subsided.

For Phase D of the trial exclusion criteria 1 and 4 will no longer apply: exclusion criteria 1 is no longer relevant as it not a consideration in MOH recommendations for COVID-19 booster vaccination, and exclusion criteria 4 because of the broad recommendations from MOH for keeping up to date with COVID-19 boosters.

### 3.5. Withdrawal Criteria

The participant may be withdrawn prematurely from the trial if he/she withdraws consent to participate in the study. In such instances, the withdrawal will be applicable to both data collection as well as vaccination.

Participants may voluntarily decline the booster vaccination, or they may be withdrawn by their attending physician and/or by the study investigator(s) on the basis of the participant's best interest. Even if the participant did not receive the booster vaccination, collected samples will still be analysed up until the point the participant withdraws consent.

All participants, including those who declined the booster vaccination, will be followed up until 12 months, unless the subject withdraws informed consent or is lost to follow-up or have died.

### 3.6. Subject Replacement

Participants who drop out will not be replaced.

## 4. TRIAL SCHEDULE

The schedule of assessments and investigations is shown in Table 1:

| Trial activity                                   | Screening  | Visit 1 | Visit 2            | Visit 3             | Visit 4               | Final visit           |
|--------------------------------------------------|------------------------|---------|--------------------|---------------------|-----------------------|-----------------------|
|                                                  | Day -28 to 0           | Day 0   | Day 7
(±2 days) | Day 28
(±7 days) | Day 180
(±14 days) | Day 360
(±14 days) |
| Enrolment                                 |                        |         |                    |                     |                       |                       |
| Informed consent                     | X                      |         |                    |                     |                       |                       |
| Eligibility                                      | X                      |         |                    |                     |                       |                       |
| Demographics                                     | X                      |         |                    |                     |                       |                       |
| Medical history                                  | X                      |         |                    |                     |                       |                       |
| Study intervention                        |                        |         |                    |                     |                       |                       |
| Confirmation of eligibility                      |                        | X       |                    |                     |                       |                       |
| Randomisation                        | X                      |         |                    |                     |                       |                       |
| Vaccination                          |                        | X       |                    |                     |                       |                       |
| Study procedures                          |                        |         |                    |                     |                       |                       |
| Physical examination                 | X                      | X       | X                  | X                   |                       |                       |
| Vital signs                          | X                      | X       | X                  | X                   | X                     | X                     |
| Pregnancy test                       |                        | X       |                    |                     |                       |                       |
| Medical review                                   | X                      | X       | X                  | X                   |                       |                       |
| COVID-19 infection review            |                        | X       | X                  | X                   | X                     | X                     |
| AE evaluation                        |                        |         | X                  | X                   |                       |                       |
| SAEs, AEs of special interest (e.g. myocarditis, |                        |         |                    |                     |                       |                       |

|                                                        |   |                 |   |   |   |   |
|--------------------------------------------------------|---|-----------------|---|---|---|---|
| pericarditis), medically attended AEs                  |   |                 |   |   |   |   |
| Safety laboratory (Phase A-C only) |   |                 |   |   |   |   |
| Haematology                               | X |                 | X |   |   |   |
| Liver and renal panel                     | X |                 | X |   |   |   |
| Cardiology panel                          | X |                 | X |   |   |   |
| Research laboratory                             |   |                 |   |   |   |   |
| Blood samples for immunogenic analysis    | X | X  | X | X | X | X |

